# Efficacy of acupuncture on cognitive function in poststroke depression: study protocol for a randomized, placebo-controlled trial

**DOI:** 10.1186/s13063-022-06011-7

**Published:** 2022-01-28

**Keywords:** Poststroke depression, Acupuncture, Efficacy, Cognitive function, Randomized controlled trial, Clinical trial

## Abstract

**Introduction:**

Poststroke depression (PSD) is the most common mental complication after stroke and has a serious impact on functional outcomes and quality of life. Antidepressants are the first-line treatment for PSD, but many reported side effects remain. Clinical research has shown that acupuncture has a positive effect on PSD. This trial aims to study the efficacy and safety of acupuncture for PSD and to explore its effect on cognitive function. It is hypothesized that acupuncture treatment improves depressive symptoms, cognitive behavior, and negative emotion processing bias in PSD.

**Methods:**

In this randomized, placebo-controlled, single-blinded trial, fifty-six people with PSD will be randomly allocated into the intervention (*n*=28) or control (*n*=28) groups. The intervention group will receive acupuncture treatment, and the control group will receive sham acupuncture treatment, in 20 sessions over 4 weeks. The primary outcome is the change from baseline in the Hamilton Depression Scale-17 (HAMD-17) scores at week 4. Secondary outcomes include the Wisconsin Card Sorting Test (WCST) and latency and amplitude of P1, N170, and P3 of the event-related potentials (ERPs) components to assess the changes in cognitive function and electroencephalography. Outcomes are assessed at baseline and post intervention.

**Discussion:**

Acupuncture therapy could become an alternative treatment for PSD, and it is expected that this trial will provide reliable clinical evidence for the future use of acupuncture for the treatment of PSD.

**Trial registration:**

Chinese Clinical Trial Registry ChiCTR1900026948. Registered on 27 October 2019.

**Supplementary Information:**

The online version contains supplementary material available at 10.1186/s13063-022-06011-7.

## Introduction

Stroke is one of the most devastating diseases affecting the aging population in the world and is the main cause of death and disability [1]. Poststroke depression (PSD) is the most frequent emotional disorder resulting from stroke and is characterized by hopelessness and loss of interest and pleasure beyond stroke symptoms. Approximately 33% of stroke survivors suffer from depression [2], which is 4 to 10 times the incidence observed in the general population [3]. PSD not only increases the risk of stroke recurrence [4], but also affects functional outcomes and quality of life [5]. Moreover, the mortality rate in stroke survivors with PSD is 3 to 4 times higher than that in stroke survivors without depression [6]. Although stroke is the direct cause of PSD, the underlying mechanisms of PSD remain unclear. At present, the diagnosis of PSD is mainly based on clinical manifestations combined with scale assessments, as there is a lack of physiological indicators. As approximately one-third of stroke patients experience aphasia [7], 70% of stroke survivors have cognitive impairment [8]. It is difficult to know whether emotion and interest have changed, which poses a great challenge in the treatment of PSD.

Pharmacotherapy is the first-line treatment of PSD. However, antidepressants are ineffective in approximately 40% to 60% of patients [9], and 30% of patients develop refractory depression due to ineffective treatment with multiple antidepressants [9]. In addition, several antidepressants increased the risk of cardiovascular disease and stroke [10], resulting in a low treatment compliance rate. Therefore, there is an urgent need for therapy that is effective, safe, and easy to promote.

Acupuncture is recommended as a promising nonpharmaceutical therapy for major depressive disorder (MDD). Published literature [11] indicates that acupuncture could improve the symptoms of depression evidenced by reductions in Hamilton Depression Scale (HAMD) scores in individuals with PSD. An fMRI study demonstrated that acupuncture may have an antidepressant effect by regulating emotion-related brain areas such as the amygdala and anterior cingulate cortex [12]. Several meta-analyses and systematic reviews have shown that acupuncture may be superior to antidepressants in alleviating the depressive symptoms of PSD [11, 13]. However, these trials did not consider placebo or sham acupuncture treatment to exclude the psychological effects of acupuncture.

Studies have shown that depression is associated with cognitive control deficits with regard to emotional information [14]. MDD is characterized by abnormal cognitive processing of negative bias, which is manifested by paying excessive attention to negative emotional information [15, 16]. The cognitive processing bias of negative emotions penetrates the whole process of depression and is at the core of the development of depressive symptoms. It is very important to understand the effects of acupuncture on cognition as it relates to PSD because understanding the relationship between emotions and cognitive function can help to explain the antidepressant effects. Event-related potentials (ERPs) reflect neural activities in the cognitive process, and because their assessment is noninvasive and has high time resolution (milliseconds), ERP measurements have become the preferred technology for studying neurocognition. According to a recent study, the recurrence and severity of depression may disrupt emotional processing, and the ERP component may be a potential biomarker to predict depression and cognitive function [17]. Thus, ERP can be adopted to explore the effect of acupuncture treatment on the negative emotion processing bias in PSD.

This randomized, placebo-controlled, single-blinded study was designed to explore the efficacy and safety of acupuncture on PSD and to explore its effect on cognitive function. It is hypothesized that acupuncture treatment will improve symptoms of depression, cognitive function, and abnormal negative emotion processing bias in individuals with PSD.

## Methods

### Study setting

This randomized, placebo-controlled, single-blinded trial will recruit 56 stroke survivors with depression. The framework of the trial is superiority. This study will be conducted at the Department of Acupuncture of The Secondary Medical College of Guangzhou University of Traditional Chinese Medicine, China. The study protocol was registered at the Chinese Clinical Trial Registry (ChiCTR1900026948). The study will be performed in line with the Declaration of Helsinki formulated by the World Medical Association. Written informed consent will be obtained from all participants. All routine interventions will be performed by hospital acupuncture staff. Figure 1 shows the CONSORT flowchart of the trial. This protocol was organized based on the Standard Protocol Items: Recommendations for Interventional Trials (SPIRIT) Checklist (Additional file 1) [18]. Figure 2 shows the SPIRIT outline for enrollment, interventions, and assessments.

**Fig. 1 Fig1:**
[figure not shown]
Flow diagram of the study procedure. CC, categories completed; TE, total errors; PE, perseverative errors; NRPE, nonperseverative errors

**Fig. 2 Fig2:**
[figure not shown]
Standard Protocol Items: Recommendations for Interventional Trials (SPIRIT) schedule of enrolment, interventions, and assessments. HAMD, Hamilton Depression Scale; WCST, Wisconsin Card Sorting Test; ERP, Event-related potential

### Eligibility criteria

#### Inclusion criteria

The inclusion criteria are as follows: (1) patient meets the criteria for “stroke” and “depression” based on the ICD-10 and are diagnosed with PSD by a psychiatrist; (2) the patient is aged between 40 and 75 years old; (3) ischemic stroke was confirmed by computed tomography (CT) or magnetic resonance imaging (MRI); (4) patient shows syndromes of liver stagnation based on traditional Chinese medicine (TCM) diagnostic criteria; (5) patient has a HAMD-17 score ≥17; and (6) the duration of PSD is less than 6 months. For the TCM diagnostic criteria, we refer to “Expert Consensus of Diagnosis and Treatment of Major Depression with Integrated TCM and Western Medicine” [19].

#### Exclusion criteria

The exclusion criteria are as follows: (1) massive cerebral infarction; (2) suicidal tendency as evaluated by psychiatrist; (3) serious medical diseases, such as brain injury, epilepsy, malignant tumor, congestive heart failure, respiratory failure, renal failure and atrial fibrillation; (4) previous head trauma history, such as coma, vomiting, amnesia, convulsions or medical emergency after injury; (5) severe cognitive impairment (Mini-Mental State Examination ≤21 [20]); (6) schizophrenia, anxiety or other mental disorders; (7) a DSM-IV history of substance abuse or dependence in the 6 months prior to assessment; and (8) metal implants in the body, such as pacemaker and deep brain stimulator.

#### Termination criteria

The termination criteria are as follows: (1) serious adverse reactions or aggravation occurred during the study, and it is not advisable to continue participating in the study; (2) those who withdraw during the study; and (3) those who do not follow the treatment for personal reasons or reject to continue the study.

### Intervention

The enrolled PSD participants receive basic treatment for stroke: basic pharmacotherapy treatment for ischemic stroke and other diseases (such as hypertension, coronary heart disease, and diabetes), and physical therapy and occupational therapy for motor dysfunction will occur every day over 60 min (including preparation). Participants cannot receive antidepressant medication, or on any other acupuncture treatments that may affect the evaluation of the efficacy of the interventions of the study. The participants’ psychological condition will be closely monitored by a psychiatrist throughout the study period. Participants would be withdrawn from the study should any sign of deterioration in mental health condition and will be treated by a psychologist. The acupuncture group will receive acupuncture treatment, and the control group will receive sham acupuncture treatment. The participating physicians in the trial are acupuncture doctors at the Secondary Medical College of Guangzhou University of Traditional Chinese Medicine. As the acupuncturists are responsible for the acupuncture treatment, they are all highly qualified, have a master’s degree in acupuncture and moxibustion, have undergone training in a unified standardized operation plan. Acupuncture treatment will be administered in the supine position, and the temperature of the treatment room is maintained at 26 °C. Participants will receive 20 treatment sessions over a 4-week period at a frequency of 5 times per week.

#### Acupuncture group

Participants in the acupuncture group will receive acupuncture at Baihui (GV20), Yingtang (GV29), Hegu (LI4, bilateral), and Taichong (LR3, bilateral). Disposable stainless-steel needles (0.3 × 40 mm; Suzhou Tianxie Acupuncture Instruments Co., Ltd., Suzhou City, China) will be used. After skin disinfection, sterile adhesive pads will be placed on the acupoints. For GV20 and GV29, acupuncture needles will be inserted through the adhesive pads for approximately 15 mm at an angle of 15°. For bilateral LI4 and LR3, the needles will be inserted vertically to a depth of 20 mm. Following needle insertion, the acupuncturists will twirl the needle handles back and forth to achieve the sensation of achiness, heaviness, and numbness (known as de qi) at all acupoints. The needles will be removed after 20 min.

#### Control group

Participants in the control group will receive sham acupuncture at the same acupoints. In the sham acupuncture group, placebo needles with a blunt tip (0.3 × 40 mm; Suzhou Tianxie Acupuncture Instruments Co., Ltd., Suzhou City, China) and sterile adhesive pads will be used. Those non-invasive placebo devices have been applied in published randomized controlled trials (RCTs) to minimize the physiological effects of skin penetratio n[21]. Furthermore, it was suggested that when applying these placebo devices as control, even acupuncture-experienced participants could be blinded when the application was in a less sensitive poin t[22]. After skin disinfection, sterile adhesive pads will be placed on the acupoints. Then, placebo needles are needled through the pads pressed against the skin without penetration. The procedures and other treatment parameters will be the same as those in the acupuncture group, e.g., the needles will be left in place for 20 min, but there will be no acupuncture needle manipulation.

### Follow-up

To evaluate the persistence of the effects, a follow-up assessment will occur 1 month after the end of the 4-week treatment.

### Outcome measures

The endpoints will be evaluated at baseline (before intervention), week 4 (immediately after intervention), and week 8 (1-month follow-up). We include two figures to show the participant timeline more clearly (see Figs. 1 and 2).

#### Secondary outcomes

The secondary outcomes include the Wisconsin Card Sorting Test (WCST) and the latency and amplitude of the ERP components P1, N170, and P3 at week 4.
The WCST [24] is being adopted to assess cognitive function. Participants are required to match response cards to the four stimulus cards along one of the three dimensions (color, form, or number) by pressing one of the 1 to 4 number keys on the computer keyboard. The measured variables include categories completed (CC), total errors (TE), perseverative errors (PE), and nonperseverative errors (NRPE).ERP

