##### ERP data

During the cognitive task, ERP data will be recorded by the NeuroScan ERP system (NeuroScan Company, American), which contains a 64-channel amplifier and a 64-electrode Ag/AgCL scalp cap. Each epoch following the emotional-face cue and target will mainly be analyzed by an off-line analysis using MATLAB 2013a (The Mathworks, Natick, USA) as well as its toolbox ERPLAB toolbox (http://www.erpinfo.org/erplab). The latency and average amplitudes of the three ERP components P100, N170, and P300 will be recorded and have been detected in various stages of attention processing.

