### Sample size

The study uses the HAMD-17 as the primary outcome measure for sample size calculation. The sample size was calculated using the following formula for the comparison of two samples:
$$ n=\frac{{\left({Z}_{1-\frac{a}{2}}+{Z}_{1-\beta}\right)}^2\times \left({\sigma}_1^2+{\sigma}_2^2\right)}{\delta^2} $$

In this study, a two-tailed test was chosen; σ_1_ and σ_1_ represent the difference in the change in HAMD-17 scores after treatment in the test group (acupuncture group) and placebo group (control group), respectively, and δ represents the difference between the two groups. Power Analysis and Sample Size software (PASS; version 11; NCSS Statistical Software, Kaysville, UT, USA) was used for sample size calculation. According to the results of a pilot study [26], σ_1_=9.50, σ_2_=7.42, δ=2.08, *α*=0.05, $$ {Z}_{1-\frac{a}{2}} $$=1.96, *β*=0.1, and *Z*_1 − *β*_=1.28. The calculated sample size of each group was approximately 22 individuals to achieve a power of 0.90 at a significance level of 0.05. After accounting for an anticipated dropout rate of 20%, the total number of patients required for this trial was 56, with 28 in each group.

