### Statistical analysis

Descriptive statistics will be used to describe demographic data of sample groups, while the normality of the distribution of each parameter will be checked by histogram and the Kolmogorov-Smirnov test. The continuous variables will be presented in mean and standard deviation (SD). A chi-squared test will be used to assess sample characteristics and gender. The data that conform to normal distribution will be analyzed by one-way analysis of variance, while the nonconforming data will be analyzed by Mann-Whitney *U* test. The latency and amplitude of the ERP data will be analyzed by mixed-effect model analysis, the Greenhouse-Geisser adjustment will be applied to adjust the degrees of freedom if the assumption of Mauchly’s test of sphericity is not significant. *P* < 0.05 will be taken as the standard for a significant difference. Data analysis will follow the intention-to-treat principle including participants who are randomly assigned. Missing data will be input with the last observation carried forward method.

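### The claim of improved cognitive function rests on ten unranked secondary measures at an unadjusted P < 0.05, with no single measure named to decide it

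*Protocol article*

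**What the plan says.** The title of the protocol article asks about efficacy on cognitive function. The Introduction states the hypothesis that "acupuncture treatment will improve symptoms of depression, cognitive function, and abnormal negative emotion processing bias in individuals with PSD". The single primary outcome, under Primary outcome, is the HAMD-17 change at week 4, which is a depression scale.

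Cognition is therefore addressed only under Secondary outcomes. There the WCST "is being adopted to assess cognitive function", and "The measured variables include categories completed (CC), total errors (TE), perseverative errors (PE), and nonperseverative errors (NRPE". The same section lists "the latency and amplitude of the ERP components P1, N170, and P3 at week 4". None of these measures is ranked or named as key. The Abstract and the Discussion place the WCST and the ERP measures side by side as evidence on cognition.

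Under Statistical analysis, P < "0.05 will be taken as the standard for a significant difference". No ordering of, or adjustment across, the secondary measures accompanies that rule.

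**The concern.** The question in the title is to be answered from a list of measures, and the document does not say which of them answers it. Followed as written, one nominally significant WCST score or ERP parameter out of ten could be reported as support for the cognitive hypothesis. No result is fixed in advance as counting against it. The false-positive rate attached to the title claim is then higher than the 0.05 threshold suggests.

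A smaller point is that, by their names, total errors (TE) should be the sum of perseverative (PE) and nonperseverative errors (NRPE). If so, TE adds no independent information, and one effect on errors can appear as two findings. The document does not state this identity; it is inferred from the labels.

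**Working it through.** The document gives no error rate for the cognitive outcomes, so there is no figure to reproduce.

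**Inputs**
- WCST measures: 4 (Secondary outcomes).
- ERP measures: 3 components × 2 parameters (latency, amplitude) = 6 (Secondary outcomes; ERP data).
- Total: 4 + 6 = 10.
- Threshold: 0.05 for each test (Statistical analysis).
- Two-sided tests: the document says so only for the sample size ("In this study, a two-tailed test was chosen"). Applying it to the secondary outcomes is an assumption.
- Group size in the simulation: 28 per group (Sample size).

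**Independent tests, no true effect.** The chance of at least one nominally significant result among k tests is 1 − 0.95^k in either direction, and 1 − 0.975^k in the favourable direction only.
- Ten measures: 1 − 0.95^10 = 40.1%; favourable 1 − 0.975^10 = 22.4%.
- Four WCST scores: 1 − 0.95^4 = 18.5%; favourable 1 − 0.975^4 = 9.6%.

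**Correlated measures.** The ten measures were simulated with 28 per group, 40,000 runs per setting, TE set equal to PE + NRPE, and one common correlation among the other nine. The correlation is assumed, because the document gives none.

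| Common correlation | At least one, either direction | At least one, favourable |
|---|---|---|
| 0 | 38% | 21% |
| 0.3 | 34% | 17% |
| 0.5 | 27% | 14% |
| 0.8 | 17% | 8% |

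The nominal rates for one test are 5% and 2.5%. Setting TE equal to PE + NRPE lowers the rate slightly, from 40% to 38% at zero correlation.

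**Direction of benefit.** The favourable-only figures need a known direction for every measure. The document states none for the ERP latencies and amplitudes. If the WCST counts only in the favourable direction and the ERP measures in either, independent tests give 1 − 0.975^4 × 0.95^6 = 34%.

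**After the change.** One named measure at two-sided 0.05 has error 5% (2.5% favourable). Under Holm across four scores, the smallest p-value is compared with 0.05/4 = 0.0125. With independent tests and no true effect, the chance of any rejection is 1 − 0.9875^4 = 4.9%.

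**The case against.** The strongest reply is that these are secondary outcomes, that the stated aim is to explore the effect on cognition, and that ranking secondary outcomes is commonly left to an analysis plan, which is not shown here. The threshold sentence does not say that one hit will confirm the hypothesis. Much of this stands: the absence of an adjustment scheme would not be a finding by itself. But the same sentence uses the word explore for efficacy and safety too, so it does not set cognition apart, and a directional hypothesis follows it. Which measure answers the title question is a protocol-level choice.

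It can also be said that cognition does have a designated instrument, the WCST, while ERP serves the separate hypothesis on emotional bias. That is correct at the level of the instrument. It narrows the family to four scores, with 18.5% and 9.6% if independent. It does not settle which of the four scores decides, and the Discussion blurs the division by counting ERP among the cognitive indices.

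Two stronger readings are tempting and are not supported:
- A reader might infer that a chance cognitive benefit is likely. For the ten listed measures the favourable rate is at most about 22%, and even the either-direction rate stays below one half.
- A reader might multiply the six ERP measures by three face valences and by cue and target epochs, and arrive at 36 separate ERP tests and a far higher rate. The document says that epochs after both cue and target will be analysed, but it specifies a mixed-effect model for the ERP data. It does not say that each component is tested separately in each valence and epoch.

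**Conclusion.** The point holds in a limited form. The title claim depends on ten unranked secondary measures judged by one unadjusted threshold. With no true effect, the chance of at least one nominally significant result is up to 40% in either direction (about 17% to 38% in simulation at correlations of 0.8 to 0). In the favourable direction it is up to 22% (about 8% to 17% at correlations of 0.8 to 0.3). For the WCST alone it is up to 18.5% and 9.6%.

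These figures assume two-sided tests at 0.05, one test per listed measure at week 4, and a claim resting on any single hit. The correlations are assumed, and the favourable-only figures also assume a known direction for each measure. The HAMD-17 primary test is not inflated. The redundancy of TE is minor.

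**What to change.** In Secondary outcomes and Statistical analysis, do one of the following before unblinding:
- name one WCST score at week 4 as the key cognitive measure and state its direction of benefit; the choice is the investigators', and perseverative errors, with fewer counting as benefit, is only an example; or
- keep all four WCST scores and apply Holm across them.

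Label the other WCST scores (under the first option) and all ERP latencies and amplitudes as supportive or exploratory. State that any claim of improved cognitive function will rest only on the key, or Holm-adjusted, result. Making the cognitive test conditional on HAMD-17 is not needed for this.

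The change needs no new data or patients. It does need a dated amendment reported to the ethics committee and the registry, as Data management and Trial status require. Timing matters: recruitment was scheduled to end in December 2021, and the Blinding section places unblinding at the end of the trial. If unblinding has already happened, the choice can no longer be presented as made in advance, and the cognitive results should be reported as exploratory.

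The cost is that isolated nominal WCST or ERP hits can no longer be claimed as confirmation. A single named score may also miss an effect that shows on another score. Holm avoids that dependence on one score, but sets a stricter first threshold.
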